It has been shown that the cure rate for tuberculosis is related to adherence to tuberculosis treatment and inversely related to HIV prevalence in the population, and to the prevalence of multi- or ultra-treatment-resistant cases [14]. According to actors in the field, one of the main causes of the low cure rate in Cameroon is non-adherence to treatment by tuberculosis patients. Also, according to these local actors, this failure in adherence itself could be due to a lack of communication and interactions between health staff and patients during the care process.

There has been a continuous expansion of mobile technologies across the world (for example, 95% of the world’s people are expected to have a mobile telephone by 2014), including developing countries. The increased use of mobile technology, such as the Short Message Service (SMS), has significant potential for health systems, and is termed mobile health (mHealth) [15,16]. SMS-based interventions involving health staff and patients can contribute to the improvement of health process and clinical outcomes [17,18]. The interventions are cost-effective both in urban and rural settings [19]. Many studies have explored the potential of mHealth (such as SMS reminders) for health objectives in the antiretroviral treatment of HIV [20-24]. Some of these interventions have been effective in improving adherence to antiretroviral treatment [23,24] and reducing viral load [23]. Effects have been observed in the prevention of HIV transmission from mother to child [25] on the adherence of health staff to guidelines for the management of malaria [26,27] and its control [28], and for the management of drug stocks [29].

For tuberculosis, studies have shown the utility of mobile phones. For example, they can be used to transmit laboratory images and results to improve notification and to reduce delays in the management of tuberculosis [30]. They can be used in the care of distant patients, as well as in the training of health staff [31]. Quite a number of studies have explored the possibility of using SMS to improve adherence to tuberculosis treatment [16,32] but none to date have looked the effect of the cure rate.

The aim of this study is to explore the potential of SMS-based reminders to improve adherence to tuberculosis treatment and to increase the cure rate in Cameroon, where adherence remains suboptimal because of a non-exhaustive implementation of DOTS.

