### Sample size

Presently, the cure rate for tuberculosis with the DOTS strategy is around 65% [2] in Cameroon, about 20% lower than the objective fixed by PNLT. Our hypothesis is that the cure rate in the SMS intervention group will reach 85%. For an attribution ratio of 1:1 in the two groups, 80% power, an alpha error of 5% and a two-sided test (effects may be interpreted independent of the way they go), we require a sample size of at least 166 participants [39], 83 in the SMS intervention group and 83 in the control group. Considering that the risk of loss to follow-up at the end of the study is important, we increased the sample size by 20%, giving 199 participants. Also, for the urban zone, we estimated that at least 90% of eligible people will have mobile phones and that at least 80% of them will consent to take part. The total number of eligible participants was therefore increased by 10% and another 20%, leading to a total of 260 participants.

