### Plan for data analysis

The results of this study will be reported following CONSORT standards [40] on randomized trials. A data entry mask developed using the Epi Data Entry program by the main investigator will be used to enter and control the quality of patient data. Analysis of the primary outcome will use the intention-to-treat approach, which includes all participants in their initial study group allocation. All participants for which there are no smear test results at 6 months will be considered not cured or cured (worst case or best case scenario). Results will be presented depending on the type of variable: means (± standard deviation) and medians (minimum and maximum) for continuous variables and percentages for categorical or binary variables.

The two groups will be described according to their baseline characteristics. Student’s test (*t*-test) will be used to calculate the difference between the two groups for continuous variables while the chi-square test will be used for categorical or binary variables. The association between study groups and cure rate will be analysed using a logistic regression model reporting the odds ratio and 95% CI.

Each individual characteristic, such as age, sex, level of education, socio-economic category, and HIV status, will be tested for an association with the cure status in a univariate analysis of the control group. Each characteristic that is significantly related with the outcome (*P* < 0.1) will be tested using a bivariate model that includes the study group, cure status and the potential confounder. If introducing the variable changes the odds ratio by more than 10%, then the variable will be considered as a potential confounder of the association and will be used in the final multivariate model.

The data from this study will be analysed using the SPSS programme (v21.0) or STATA (v11). Comparisons between the two groups will be expressed in terms of the odds ratio and the number needed to treat. Open questions in the questionnaire (especially problems observed during follow-up) will be analysed using the content analysis technique.

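### The final adjusted model is chosen from the trial's own outcome data, so its content depends on the treatment effect; name its covariates in advance

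*Protocol article*

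**What the plan says.** The Plan for data analysis first provides an unadjusted comparison of cure: a chi-square test and a logistic model of study group giving an odds ratio with 95% CI. Table 1 lists the same two methods.

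It then sets out a search for covariates. Individual characteristics, of which age, sex, education, socio-economic category and HIV status are given as examples, "will be tested for an association with the cure status in a univariate analysis of the control group". Those with P<0.1 are added one at a time to a model with study group, and then: "If introducing the variable changes the odds ratio by more than 10%, then the variable will be considered as a potential confounder". Variables that pass enter the final multivariate model. No covariate is forced in, and the list of candidates is open.

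The Background gives 33% HIV co-infection among new smear-positive cases and describes the cure rate as "inversely related to HIV prevalence in the population".

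**The concern.** A change-in-estimate rule belongs to observational work, where a shift in the exposure coefficient signals confounding. Here patients are randomised 1:1 within centre, so a baseline difference between arms is a chance event. The shift then has two sources.

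- **Chance imbalance** in the covariate.
- **Non-collapsibility.** Adding a prognostic covariate to a logistic model moves a non-null treatment odds ratio away from 1 even when the covariate is perfectly balanced. With no treatment effect this source vanishes.

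The second source makes selection depend on how well the SMS reminders work. The rule also tends to discard prognostic covariates that happen to be balanced, although these are still worth adjusting for. At stake is the meaning of the adjusted result: its odds ratio is sometimes marginal and sometimes conditional on HIV, and its confidence interval ignores that the model was picked after the outcomes were seen.

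**Working it through.** **Inputs from the article.** Sample size section: "the cure rate for tuberculosis with the DOTS strategy is around 65" per cent; "Our hypothesis is that the cure rate in the SMS intervention group will reach 85" per cent; "For an attribution ratio of 1:1 in the two groups"; "80% power, an alpha error of 5% and a two-sided test". Background: 33% HIV co-infection. Trial status: 288 patients included, taken here as 144 per arm.

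**Assumption.** The odds ratio of HIV for cure is not in the article. I use 0.6 down to 0.2.

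**Step 1: the plan's own figure.** With mean cure 0.75 and difference 0.20:

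n = [1.96·√(2·0.75·0.25) + 0.8416·√(0.65·0.35 + 0.85·0.15)]² / 0.20² = (1.200 + 0.501)² / 0.04 ≈ 72.4, so 73 per arm.

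Continuity correction: (73/4)·[1 + √(1 + 4/(73·0.20))]² ≈ 82.7, so 83 per arm. This agrees with "we require a sample size of at least 166 participants". The design inputs are therefore read correctly.

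**Step 2: non-collapsibility with zero confounding.** Crude odds ratio = (0.85/0.15)/(0.65/0.35) = 3.05. For each arm, solve 0.67·p₀ + 0.33·p₁ = overall cure, with odds(p₁) = HIV odds ratio × odds(p₀). Example at HIV odds ratio 0.2:

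- Control: p₀ = 0.7716, p₁ = 0.4032; 0.67·0.7716 + 0.33·0.4032 = 0.650.
- SMS: p₀ = 0.9222, p₁ = 0.7034; 0.67·0.9222 + 0.33·0.7034 = 0.850.
- Conditional odds ratio = (0.9222/0.0778)/(0.7716/0.2284) ≈ 3.51.

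| HIV odds ratio | Conditional odds ratio | Shift from 3.05 |
|---|---|---|
| 0.6 | 3.09 | +1% |
| 0.37 | 3.21 | +5% |
| 0.25 | 3.38 | +11% |
| 0.2 | 3.51 | +15% |

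From about 0.25 downwards, a perfectly balanced HIV covariate crosses the 10% line and would be called a potential confounder. At 0.37 balance alone does not trigger the rule; some chance imbalance is needed as well.

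**Step 3: how often HIV enters.** Both screens were simulated with 144 per arm and 33% HIV prevalence:

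| HIV odds ratio | 65% vs 65% | 65% vs 85% |
|---|---|---|
| 0.6 | 1% | 4% |
| 0.37 | 10% | 24% |
| 0.25 | 21% | 53% |
| 0.2 | 30% | 66% |

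Separate runs differ by a few percentage points (for example 24 to 27% at 0.37 and 62 to 66% at 0.2, both at 65% vs 85%). The pattern is stable, and the same at 83 and 130 per arm.

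**Step 4: direction.** In simulations with five candidates (HIV and four unrelated covariates) at 83 and 130 per arm, whenever at least one covariate was selected, the final odds ratio lay further from 1 than the unadjusted one in 90 to 100% of trials at 65% vs 85%, and in about 62 to 77% with no effect.

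**Step 5: error rates.** With five unrelated candidates, 1 − 0.9⁵ = 41% of trials pass at least one at P<0.1. After both screens the share falls to 1.6 to 5.6% at 83 per arm and 0.2 to 1.5% at 130 per arm. Type I error of the final model is about 5 to 6.4% at 144 per arm, and 4.1 to 5.7% at the smaller sizes. With HIV pre-specified it is 4.2 to 5.2%.

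**The case against.** The strongest reply is that little is at risk. The unadjusted test and odds ratio are planned separately and do not pass through the selection. At 288 patients and 65% vs 85%, unadjusted power is already 97 to 98%, against 98 to 99% with HIV adjusted. Screening in the control arm is partly defensible, because it keeps the treatment effect out of the first step. All of this stands, and it limits the point to the adjusted analysis.

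The reply also disposes of several stronger readings that a reader might infer:

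- **That error rates are seriously distorted.** Step 5 shows slight inflation at most.
- **That the model fills with chance covariates.** They often pass the first screen but seldom both.
- **That HIV is usually omitted.** This holds for HIV odds ratios of 0.37 to 0.6. At 0.25 with the planned effect it is about even, and at 0.2 HIV usually enters. The article gives no effect size to settle it.
- **That HIV is an established patient-level predictor in this trial.** The Background statement is about populations, and the 33% refers to new cases generally, whereas hospitalised and severely ill patients are excluded.
- **That the move from 3.05 to 3.51 is bias.** It is the difference between a marginal and a conditional odds ratio, and pre-specified adjustment for HIV gives the conditional one too. The fault is that the rule switches between them according to the data.

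**Conclusion.** The concern holds for the final multivariate model only. The article fixes an outcome-dependent rule, so this is a stated choice and not a detail left to an analysis plan. Under the assumptions of 33% HIV prevalence, 144 per arm and 65% control cure, the chance that HIV is in the model roughly doubles when the planned effect is present: from 10% to 24% at an HIV odds ratio of 0.37, and from 30% to 66% at 0.2. The adjusted odds ratio and its CI therefore come from a model that cannot be known in advance and tends to lie further from 1 than the unadjusted result. At 0.37 to 0.6 the rule usually drops the one listed characteristic that the Background itself marks as relevant. The unadjusted comparison is unaffected and the type I error cost is small. This is a worthwhile, inexpensive correction and not a threat to the trial's primary test.

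**What to change.** Delete both the P<0.1 step and the 10%-change step. Pre-specify one adjusted logistic model with study group, HIV status, age and sex, reported whatever their significance, beside the unadjusted result.

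Centre is the randomisation stratum and should be accounted for, but not by fixed effects. With 12 to 16 centres these cost 11 to 15 parameters. Added to the four terms above, that makes 15 to 19 parameters against about 72 non-cures (144·0.35 + 144·0.15 = 72), or roughly 4 to 5 events per parameter. Mantel-Haenszel stratification for the comparison without covariates, and conditional logistic regression or a random centre intercept for the adjusted model, avoid this.

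The cost is wording, settled before database lock; the sample size does not change. Two things need attention: a rule for missing HIV status, and confirmation that HIV status is recorded at all. The Data collection section does not list it, although the Plan for data analysis intends to use it.

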### Ethical considerations

This study strictly respects the ethical principles of the Helsinki declaration [41] and local recommendations for medical research. The protocol was submitted to the National Ethical Committee of Cameroon and has been approved. It also received administrative authorisation from the Ministry of Public Health of Cameroon. All eligible participants will be contacted by health staff involved in the study. Before signing the consent form, they will receive key information on the study: objectives, data collection, expected results, duration, benefits, voluntary character, the right to withdraw at any time, confidentiality, use of data and results obtained. Data from participants collected by health staff and the secretary will be treated as confidential and retained in their health records. Patient telephone numbers will be used only for sending SMS messages and will not be communicated to any person not involved in the study. SMS messages will be strictly confidential. The results of the study will be published respecting the strict anonymity of all participants. Patients will be informed on the main results of the study through SMS messages. Continuous training and information sessions will be organised for collaborators regarding the results of the study. At the end of the study, the list of SMS message sent and patient health records will simply be destroyed. They will not be used for any other purpose.

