**Secondary**			
**Adherence of patients to treatment (second, fifth, sixth months)**			
Drug prescriptions collected and doses taken (visual analogue scale)	Percentage of adherence to treatment during the last 30 days	Continuous	*t*-test
Keeping appointments		Binary	Chi-square
Punctuality of appointments		Categorical	Chi-square
**Multi-drug-resistant tuberculosis (fifth and sixth months)**	Percentage of patients with multi-drug-resistant tuberculosis	Binary	Chi-square
**Satisfaction (sixth month)**	Satisfaction	Continuous	*t*-test

The status of each patient will be based on the results of smear tests carried out in the second, fifth and sixth months in the treatment centre. At the fifth month, two scenarios are possible. If the smear test is negative, treatment continues during the sixth month. At 6 months, the final smear test is done to see if the patient is cured. If this test is negative, the patient is classified as cured.

If the test at 5 months is positive, a second smear test will be performed to confirm the result (which is not mandatory for this study). At this moment, the patient will be considered as a treatment failure and classified as not cured in the study.

Participants lost to follow-up or referred to other treatment centres, will be considered cured (best case) or not cured (worse case) as two extreme statistical scenarios.

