### Data collection

Health staff taking care of participants in the study will collect data using patient follow-up files developed by the research team. These will contain all the necessary questionnaires, scales and lists of problems. The follow-up files will be kept with the participants’ health records. A marker will be placed on the file of each participant to reduce the risk of them being ‘forgotten’ by health staff during the study. Forms in the file will be completed in French for each visit (the day of inclusion and the second, fifth and sixth months).

Before the onset of recruitment, a meeting will be held with the staff members of the treatment centres. This will inform them of and validate the strategies for the implementation of the study (inclusion of participants, collection of data, use of VAS by patients to evaluate adherence, transmission of data and so on).

During the recruitment phase, a secretary will be responsible for collecting telephone numbers from the participant study files twice a week from each Treatment and Diagnostic Centre. These will be entered into the SMS database. The secretary will also collect socio-demographic data (from the day of inclusion), smear test results (from the day of inclusion, and the second, fifth and sixth months), punctuality data and results of resistance to rifampicin tests (Genexpert).

At least two sessions to supervise staff members (2 months and 6 months after the onset of recruitment) will be carried out in each centre so that data collection remains effective and consistent. Treatment centres facing problems will receive additional training and supervision at appropriate intervals. After recruitment, the secretary will collect data once a week to keep statistics and participant registers up to date. At the final follow-up (during the third visit at the end of the sixth month), health staff will administer a self-evaluation questionnaire on the degree of satisfaction to the participants.

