### Material and equipment for sending SMS messages

A proprietary application will be used to send regular SMS messages to participants through the web [42]. The program logs SMS messages and produce reports of those sent.

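### The plan orders patient health records and the list of SMS messages sent to be destroyed at study end, which removes care files and the source documents for the primary outcome and for message sending

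*Protocol article*

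**What the plan says.** Three sections of the Protocol article bear on this.

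- **Ethical considerations.** On where the data sit: "Data from participants collected by health staff and the secretary will be treated as confidential and retained in their health records". Later in the same paragraph: "At the end of the study, the list of SMS message sent and patient health records will simply be destroyed". The article gives no retention period, no exception and no archived copy.
- **Data collection.** "The follow-up files will be kept with the participants’ health records". The follow-up files are forms designed by the research team. For the period after recruitment, "the secretary will collect data once a week to keep statistics and participant registers up to date".
- **Material and equipment for sending SMS messages.** "The program logs SMS messages and produce reports of those sent".

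The Intervention group section adds that side effects, adherence problems, problems receiving messages and their solutions are written into the health record by health staff, and into a daily log by the secretary.

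**The concern.** This is a stated rule, so it cannot be put down to detail that a condensed article leaves out. Two things are at stake.

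The first is patient care. The health record holds clinical information that is not specific to the trial. The plan expects some participants to be smear-positive at month 5, to be classed as treatment failures and to be tested for rifampicin resistance. The Background section itself names relapse, drug resistance and prolonged treatment as consequences of irregular adherence. A study rule that removes the care file of such patients goes beyond protecting trial confidentiality.

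The second is verification. The primary outcome is a smear result obtained in routine care at up to 16 centres and copied onward by a secretary. The exposure is whether daily messages went to the allocated arm. The rule removes the documents that would let anyone check either of these later. The main investigator both runs the randomisation (Randomisation) and builds the data entry system (Plan for data analysis), so an independent check against source has particular value here.

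**Working it through.** The article gives no figure on this point, so the check is to set its sections against each other.

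1. **What is to be destroyed.** Ethical considerations names two items: the list of messages sent and the patient health records.

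2. **Whether the health records could simply mean the study forms.** Data collection names the follow-up files and the health records as two things, one kept with the other. The Intervention group section has health staff record clinical problems and solutions in the health record. On the article's own usage, the health record is the clinical file.

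3. **What the records support.** The text below Table 1 says: "The status of each patient will be based on the results of smear tests carried out in the second, fifth and sixth months in the" (the sentence ends by naming the place of care). Ethical considerations says that data collected by health staff and by the secretary are kept in the health records. Those records are therefore source documents for the primary outcome.

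4. **What the SMS list supports.** It is a report of messages sent. It can show that messages went out, and to whom. Nothing says that it records delivery or reading.

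5. **What is not ordered destroyed.**
   - The secretary's statistics and participant registers (Data collection).
   - The secretary's daily log (Intervention group).
   - The electronic database of participants' data (Plan for data analysis): "A data entry mask developed using the Epi Data Entry program by the main investigator will be used to enter and control the quality".

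   These are copies or secondary records. They allow the entered data to be analysed again, but they cannot show whether an entry matches the original.

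6. **Timing.** Study design gives 4 months of recruitment and 8 of follow-up, 12 in all. Assume that treatment starts at enrolment and that the study ends at month 12. A month-5 failure is then classified between study month 0 + 5 = 5 and study month 4 + 5 = 9. That is 12 − 5 = 7 to 12 − 9 = 3 months before study end.

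7. **Scale.** Read as written, the rule covers every included participant, 288 according to Trial status. For the number not counted as cured, assume 144 per arm and the planned cure rates of 65% and 85%:
   - control: 144 × 0.35 = 50.4
   - SMS: 144 × 0.15 = 21.6
   - total: 72

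   With the planned 260 participants (130 per arm), the total is 130 × 0.35 + 130 × 0.15 = 45.5 + 19.5 = 65. If both arms stayed at 65%, it is 288 × 0.35 = 100.8, about 101. Each count includes deaths, transfers and losses to follow-up, so under its own assumed rates it is an upper guide to the number still ill.

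**The case against.** The strongest reply is that the wording is loose. The sentence comes among assurances of confidentiality and is followed by a promise that the material will serve no other purpose, which suits material held by the study. The same paragraph says that data collected by the secretary are kept in the health records, so the term may stand for the study file there. Care itself belongs to the national programme. This reading is possible, but Data collection separates the two kinds of file, and a centre has only the text to follow. If only the study files were meant, the care file would be safe but the trial's source documents would still go.

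A second reply is that retaining data and then destroying them at study end can be two steps in sequence. That stands: the two sentences do not strictly contradict each other. The problem is the destruction rule itself.

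A third reply concerns stronger readings that the article does not support:

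- A reader might infer that the only source for the primary result disappears and that no re-analysis would be possible. The database, registers and daily log are not listed for destruction. The article does not say whether laboratory or programme registers also hold the smear results.
- A reader might infer that evidence of message delivery is lost. The log is described as covering sending only, and problems with reception also go into the daily log.
- A reader might infer that a null result could not be explained. Self-reported adherence, appointment data and recorded problems are all to be analysed under the plan. Nothing says that records are destroyed before analysis.

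**Conclusion.** The point holds in limited form. As written, the plan removes the care files of participants, including those classed as failures or found resistant after month 5. It also removes the source documents for the smear-based outcome and the record of messages sent to each arm. Re-analysis of entered data remains possible; verification against these documents does not.

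Under the literal reading all 288 files are affected. The figure of about 72 not counted as cured rests on equal arms and the planned cure rates, and it is not a count of patients still ill. The conclusion assumes that the term health records carries the meaning it has in Data collection. Allocation, outcome definition, estimate and error rate are all unaffected. The sentence still needs replacing, because destruction cannot be undone. Trial status reports that recruitment has stopped but not that anything has been destroyed, so as far as the article shows the loss can still be prevented.

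**What to change.** Replace the destruction sentence in Ethical considerations with a paragraph stating that:

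- patient health records are excluded from destruction and stay with the treatment centre;
- the study follow-up files and the log of SMS messages sent are archived confidentially for a retention period that the sponsor states;
- only the link between telephone number and study identifier is deleted, after database lock and after the main results have been sent to participants by SMS, as the same section plans.

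The cost is a one-paragraph amendment and secure storage for about 288 study files and one electronic log. No extra patients or staff are needed. The small downside is that confidential data are held longer; deleting the telephone link limits this.
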